##### Subgroup analysis

Recognising that the trial is not powered to detect effect differences in subgroups, we will conduct exploratory subgroup analyses for the primary outcome to determine if the intervention effect varies by baseline characteristics. The pre-specified subgroups are: age (split at the median); marital status (married/not married); number of children (0/1+); residence (city/other); occupation (in education/other); highest education level completed (university/other) and pregnancy intention (wants to avoid/other). Within the pre-specified subgroups, we will assess heterogeneity of treatment effect with a test for interaction [73–77]. Interaction test *p* values will be presented but will be interpreted with caution due to the exploratory nature, the multiple tests performed and of the low power of the interaction test. We will estimate odds ratios along with 95% CIs for each subgroup without *p* values. As this is an exploratory analysis of potentially influential characteristics that are not justified a priori, we will not hypothesise effect directions.

##### Contamination

To assess the potential for contamination, we will report the proportion of control group participants who read another participant’s messages and the proportion of intervention participants whose messages were read by another participant.

##### Analysis of pooled trial data

We are conducting trials of similar interventions in two other countries. If the results of the other trials are available, we will conduct the principal analyses on the pooled dataset.

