## Methods

### Study design

This study is a parallel-group, individually randomised superiority trial with a 1:1 allocation ratio evaluating the effect of a contraceptive intervention delivered by mobile phone text messaging compared with control text messages about trial participation. The objective of this research is to establish the effect of the intervention on young women’s attitudes towards effective contraception in Palestine.

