### Analyses

#### General statistical considerations

The analysis of the data will follow the plan specified below. There will be no interim analyses and, therefore, no stopping rules. All analyses will be according to randomised arm and only participants with complete outcome data will be included in the primary analysis (a complete case analysis). All statistical tests will be two-sided. All effect estimates will be reported with a 95% confidence interval and its associated *p* value. Statistical significance will be considered at the 5% level. Analyses will be conducted using the latest version of Stata.

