##### Analysis of the primary outcome

The primary outcome is binary and we will compare the crude proportion reporting that at least one method is acceptable in each group. We will estimate the difference between the groups using logistic regression and will report the odds ratio along with the 95% confidence interval and its *p* value for evidence against the absence of intervention effect from the model. The primary analysis regression will be adjusted for baseline covariates likely to be associated with the outcome in order to improve the efficiency of the analysis and avoid chance imbalances [72]. These pre-specified covariates that we will adjust for are: pregnancy intention (wants to avoid/other); age (18–19/20–24 years); number of children (0/1+); highest education level completed (university/other) and acceptability of effective contraception at baseline (at least one method acceptable/no methods acceptable). We will also report the crude odds ratio between arms.

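### The conditional pooled analysis carries the single-country model onto three trials with no term for trial and no check that the effect is consistent between them

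*Protocol article*

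**What the plan says.** Under Additional analyses, the subsection Analysis of pooled trial data has two sentences. The first reads "We are conducting trials of similar interventions in two other countries". The second reads "If the results of the other trials are available, we will conduct the principal analyses on the pooled dataset".

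The model being carried over is set out under Analysis of the primary outcome, whose key sentence begins: "We will estimate the difference between the groups using logistic regression and will report the odds ratio along with the 95% confidence interval". The adjustment set is a closed list of five: pregnancy intention, age group, number of children, education, and "acceptability of effective contraception at baseline (at least one method acceptable/no methods acceptable". Trial and country are not in it, as one would expect of a list written for a single-country trial.

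Two other statements bear on the point. Study design describes this trial as an "individually randomised superiority trial with a 1:1 allocation ratio". General statistical considerations says that "only participants with complete outcome data will be included in the primary analysis (a complete case analysis"), and that the analysis will follow the plan set out in the article. The allocation ratios, sizes and outcome rates of the other two trials are not given.

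**The concern.** Women are randomised within a trial, so a pooled comparison of arms should be made within trial. The pooled analysis instead borrows a model that has no place for trial. Two things follow.

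First, the odds ratio is non-collapsible. If control rates differ between countries beyond what the five covariates explain, a model without trial estimates a more marginal odds ratio, which lies nearer 1 than the within-trial value. The Background ties acceptability closely to local conditions (stigma around premarital sex, pressure to have children early in marriage, the methods available locally), so different rates elsewhere are plausible.

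Second, the interventions are described only as similar. A single pooled odds ratio, with no trial-by-arm term and no heterogeneity statistic, cannot show whether the effect is shared or comes from one country. This second point does not depend on any assumed rate.

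**Working it through.** **Plan's own figures.** Sample size gives 50% against 65%, odds ratio 1.86, 90% power and 454 analysed.
- Odds ratio: (0.65/0.35)/(0.50/0.50) = 1.857.
- Per arm: n = [1.960·√(2·0.575·0.425) + 1.2816·√(0.50·0.50 + 0.65·0.35)]²/0.15² = 226.2, rounded up to 227, so 454 in total. Both figures reproduce.

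The article gives no figure for the pooled analysis. The rest uses 1.857 as the common within-trial odds ratio and **assumed** control rates for three trials of equal size, each randomised 1:1.

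**Step 1: no covariates, no trial term.** In trial k, p1k = OR·p0k/(1 − p0k + OR·p0k). Average p0k and p1k over the trials and take the odds ratio of the averages. For 30/50/70%, the intervention rates are 0.443, 0.650 and 0.8125, with mean 0.635. The control mean is 0.50. The pooled odds ratio is (0.635/0.365)/1 = 1.74.

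**Step 2: baseline acceptability added, as the principal model requires.** For each scenario, 1,000 pooled datasets were simulated with 454 women per trial. Baseline acceptability was drawn at the trial's control rate, with an assumed log-odds coefficient of 1.0 on the outcome. The model had arm and baseline acceptability, with and without trial indicators.

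| Assumed control rates | Step 1: no covariates | Step 2: baseline, no trial term | Log-scale attenuation in step 2 | Step 2 with trial indicators |
|---|---|---|---|---|
| 40/50/60% | 1.83 | 1.84 | 1.8% | 1.85 |
| 30/50/70% | 1.74 | 1.80 | 5.3% | 1.86 |
| 10/50/90% | 1.43 | 1.63 | 21.5% | 1.87 |

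The step 2 columns are the relevant ones, because baseline acceptability is in the planned model. Adding trial returns the estimate to about 1.857 in every row.

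**Step 3: no true effect.** With 1:1 in every trial, both arms have the same mix of countries, so the pooled odds ratio is exactly 1.00. In the simulations, rejection at the two-sided 5% level was 5.7%, 4.0% and 3.9% without trial indicators and 5.8%, 4.5% and 5.9% with them. The simulation error is about √(0.05·0.95/1000) = 0.7 percentage points, so none of these suggests inflation.

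**Step 4: what it would take to confound.** Take 285 randomised per arm per trial (570/2), rates of 30/50/70% and no effect. Let retention be 75% intervention against 85% control in the low-rate trial, the reverse in the high-rate trial, and 80% in both arms of the middle one. The analysed numbers are 214/228/242 intervention and 242/228/214 control.
- Intervention mean: (0.3·214 + 0.5·228 + 0.7·242)/684 = 0.508.
- Control mean: (0.3·242 + 0.5·228 + 0.7·214)/684 = 0.492.
- Odds ratio, without covariates: 1.07.

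This needs differential loss of 10 points in opposite directions, lined up with the country rates.

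**The case against.** The strongest reply is that two sentences in an article do not say trial will be left out. A joint or fuller analysis plan may well include it, and an article need not spell out such detail. That is fair, and it limits how hard the point can be pressed. It does not remove it: the article says which analysis will be run on the pooled data, and that analysis has a closed covariate list without trial. What is fixed does not suit the dataset.

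A second reply is that the attenuation is a change of estimand and not a bias under the null, that it is conservative, and that the planned covariates absorb part of it. All of this stands. Figures without covariates, such as 1.74, overstate the shift for the planned model.

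A third reply is that the analysis is conditional and sits under Additional analyses, so it neither replaces nor hides this trial's own odds ratio. That also stands, and it keeps the severity low.

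A reader might infer something stronger: that pooling without a trial term mixes differences between countries into the arm effect. The documents do not support this. This trial is randomised 1:1 and, if the others are too, arm is balanced across countries. Confounding would need arm ratios among the women analysed to differ between trials, through unequal allocation or differential loss in the complete-case set. Neither is shown, and Loss to follow-up already plans a comparison of loss by arm in this trial.

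**Conclusion.** The point holds, as a minor one. Read as written, the pooled analysis has no term for trial and no check of consistency across three trials of merely similar interventions. On the assumed rates, the cost in the primary-outcome odds ratio is about 2% to 5% on the log scale for moderate differences between countries (1.86 to 1.84 or 1.80). It is material only for very wide ones (1.63 at 10/50/90%). These sizes rest on equal trial sizes, 1:1 allocation, a common within-trial effect, an assumed strength of the baseline covariate, and control rates that the documents do not give. Adjustment for the other four covariates was not modelled and could reduce the shift further.

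There is no evidence of confounding by country or of an inflated type I error. The missing heterogeneity check matters whatever the rates turn out to be, because the pooled result would otherwise be hard to interpret. This trial's own primary analysis is unaffected.

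**What to change.** Add two sentences to Analysis of pooled trial data. State that the pooled model will include trial as a stratification factor or fixed effect, with the arm effect estimated within trial; or, equally acceptable, that trial-specific adjusted log odds ratios will be combined in a two-stage meta-analysis. State that the trial-by-arm interaction, or a heterogeneity statistic, will be reported with the pooled estimate. Settle this before the other trials' results are known, so that the choice cannot depend on them.

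The cost is a few model terms and a slightly wider interval on the log-odds scale. In the 30/50/70% scenario without covariates, with 227 women per arm per trial, the standard error rises from 0.1105 to 0.1172, about 6%. The estimate moves back out by more than that, so the z statistic rises from 5.02 to 5.28 and no power is lost. No data collection changes.

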### Participants’ rights and safety

Participants will have the right to withdraw at any time during their involvement, without having to give a reason. Participants can withdraw by contacting the project coordinator. Acting on participants’ requests to withdraw from the trial, participants’ status will be changed to ‘withdrawn’, the text messages will stop and the person will be excluded from the list of participants who are due follow-up. Participants will be able to stop text messages, but choose to continue with the trial follow-up. Participants’ participation and personal identifiable data will remain confidential and research data will be anonymised.

In the formative work, we explored young people’s views on confidentiality about receiving messages on their mobile phone. While the large majority of participants did not report that they were concerned about receiving messages about contraception on their mobile phone, it is possible that some participants will want to keep the messages confidential from certain people (e.g. partner, parents) and that these people might view the messages. The messages remind participants that they can delete the messages and provide instructions on how to keep the messages private. We will provide information on support services that they can contact if they feel unsafe because of the messages being read. We will review physical violence during participants’ involvement in the trial reported on the follow-up questionnaire.

## Discussion

The results of this trial will provide evidence for the effect of the intervention on young Palestinian women’s attitudes towards effective contraception. The analysis of the secondary and process outcomes may provide evidence for the effect of the intervention on the use of effective contraception, attitudes towards the individual effective methods, service use, unintended pregnancy, induced abortion and on the psychological processes hypothesised to influence contraceptive use.

There are a number of limitations of this trial. The main limitation is that the primary outcome is self-reported. As sexual activity before marriage is highly stigmatised in Palestine, this precluded the option of an objective primary outcome in the study population. We expect that a significant proportion of participants in the trial will not be married and either will not be sexually active, or will be unwilling to admit if they are. Powering a study for uptake of contraception in a population, which will likely result in a small number of outcome events, would make the sample size prohibitively large. In not married/not sexually active young women, the intervention aims to improve attitudes towards the most effective methods, so that they will find a wider range of methods acceptable if they want to choose a method in the future.

While local research staff are not made aware of allocation, there is a chance that the participants could reveal to local research staff collecting outcome data the group that they were allocated to. Staff are trained in asking questions in a standardised way. As the communities from which the trial participants derive are close, we anticipate that there will be some degree of contamination but we cannot predict the extent of it. We are measuring the potential for contamination at 4-month follow-up and will consider this when interpreting the results. In absence of further data, we have powered the trial to detect an absolute difference of 15% in the proportion of participants finding at least one method of effective contraceptive acceptable. The trial will have a lower power if the intervention has a smaller effect.

### Trial status

Recruitment commenced on 8 December 2016 and is will be complete by 31 July 2017. The estimated completion date for the final participant recruited (final data collection date for the primary outcome) is January 2018.

## Abbreviations

CONSORT: Consolidated Standards of Reporting Trials diagram
OC: Oral contraceptive pill
IUD: Intrauterine device
LSHTM: The London School of Hygiene and Tropical Medicine
PFPPA: the Palestinian Family Planning and Protection Association
IPPF: The International Planned Parenthood Federation.
MAR: Missing at random
SMS: Short messaging service
